The well-described poor prognosis of patients with overlap syndrome (i.e., the simultaneous presence of COPD and obstructive sleep apnoea syndrome [OSAS]) and the finding that patients with overlap syndrome show a faster decline of lung function (FEV1/FVC) over time than COPD patients without OSAS strongly underscore the hypothesis that intermittent hypoxemia is a major pathogenic factor in COPD development and progression [9, 10]. Further, both COPD and OSAS are associated with major cardiovascular co-morbidity which – importantly – is already detectable at early disease stages [8, 11] and is aggravated when both COPD and OSAS are present [10]. Hypoxemia, even when occurring intermittently, causes dysfunctional endothelium-dependent, NO-mediated vascular regulation in the pulmonary and systemic circulation in both diseases [12, 13]. Transient hypoxemia evokes adaptations in the pulmonary and systemic micro- and macrocirculation [14], and it changes pulmonary gene expression in a manner mimicking chronic lung diseases [15]. Therefore, intermittent hypoxemia may drive COPD progression via acting on the pulmonary endothelium, which has been named the “orchestra conductor in respiratory diseases” [16]. By this way, the pathophysiological mechanisms set off by hypoxia in the lungs are relevant drivers of pulmonary hypertension and right ventricular hypertrophy and failure on the one hand, but they also promote systemic cardiovascular disease and mortality.

Exertional hypoxemia as a model for provoking intermittent hypoxemia has been tested in several small studies using diverse exercise approaches. Traditionally, the 6-minute walk test (6MWT) has been used to test exercise capacity and exertional hypoxaemia in COPD patients [17]. Exertional desaturation during the 6MWT has been associated with rapid lung function decline [18] and high mortality rate [19]. However, a 15-second breath-hold-test (15-sec BHT) has also been proposed as an easily feasible alternative to test COPD patients for the presence of exercise-induced hypoxaemia [20]. Finally, bicycle ergometry remains the gold standard for exercise testing in clinical medicine; however, performing this test requires more sophisticated equipment and trained personnel than the 6MWT or the 15-sec BHT. Exertional hypoxaemia during bicycle ergometry has been shown to reflect pulmonary artery pressure in COPD patients [21].

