## Methods

### Study design

PROSA is a monocenter, observational, prospective cohort study. 148 patients with chronic obstructive lung disease (COPD) stages 2–3, groups B and E according to GOLD [7] will be enrolled in this clinical study. We expect that one third of our study cohort will experience exertional hypoxemia based on incidence rates reported in previous studies [22, 23]. Patients will be recalled to the study site once per year for a total of 36 months of follow-up.

The primary endpoint of the study will be the difference in FEV_1_ (LLN) over time in COPD patients with exertional desaturation versus those without exertional desaturation (exertional desaturation will be defined as oxyhemoglobin saturation by pulse oximetry (SpO_2_) < 90% or a drop of SpO_2_ ≥ 4% during a six-minute walk test [19].

Secondary endpoints have been defined as follows: (1) The difference in all-cause mortality over time in COPD patients with exertional desaturation versus those without exertional desaturation. (2) The difference in COPD-related mortality over time in COPD patients with exertional desaturation versus those without exertional desaturation. (3) The difference in frequency of hospital admissions for exacerbation of COPD in COPD patients with exertional desaturation versus those without exertional desaturation. (4) The difference in frequency of hospital admissions for causes other than exacerbation of COPD in COPD patients with exertional desaturation versus those without exertional desaturation. (5) The sensitivity and specificity of plasma biomarkers at baseline to predict the prevalence of exertional desaturation in COPD patients. (6) The sensitivity and specificity of plasma biomarkers at baseline to prospectively predict the slope of lung function decline in COPD patients. (7) The sensitivity and specificity of plasma biomarkers at baseline to prospectively predict the mortality rate in COPD patients. (8) The difference in incidence and extent of exercise hypoxemia between carriers and non-carriers of single nucleotide polymorphisms in genes of the L-arginine – dimethylarginine pathway. (9) The difference in positive and negative predictive value of bicycle ergometry, 6-minute walk test, and 15-sec breath-hold test to discriminate between COPD patients with exertional desaturation versus those without exertional desaturation.

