### Statistical analysis

Statistical analyses will be performed using the SPSS Version 27 software package (IBM Corporation, Armonk, NY, USA) and GraphPad Prism (version 6.01, GraphPad Software, San Diego, CA, USA) in the investigational center. All variables will be tested for normal distribution using the Kolmogorov–Smirnov test. Data will be expressed as mean with standard deviation (SD). Differences between groups will be tested for significance using the nonparametric Mann–Whitney U test for two groups or the Kruskal–Wallis analysis of variance for more than two groups. The Chi^2^ test will be used for comparison of categorical variables between groups. Logistic regression will be used to assess the relationship between exertional hypoxemia and mortality. The nil hypothesis for statistical evaluation of the primary endpoint will be that the difference in FEV_1_ (LLN) at 3 years of follow-up will not be different between COPD patients with exertional desaturation versus those without exertional desaturation. Exertional desaturation will be defined as oxyhemoglobin saturation by pulse oximetry (SpO_2_) < 90% or a drop of SpO_2_ ≥ 4% during a six-minute walk test [19].

Survival analyses will be performed using Kaplan–Meier curves comparing patients with or without exertional hypoxemia, and with ADMA and SDMA above or below the cut-off value determined in receiver-operated curve (ROC) analyses. Hazard ratios (HR) and 95% confidence intervals (CI) will be calculated by multivariable-adjusted logistic regression analyses. For all tests, *p* < 0.05 will be considered statistically significant. A correction of p will be performed for multiple comparisons when adequate.

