**Fig. 2 Fig2:**
[figure not shown]
Intermittent hypoxemia, as caused by co-morbid obstructive sleep apnea, has been shown to act as a driver of rapid lung function decline, systemic cardiovascular co-morbidity, and excess mortality. Exercise is another well-known trigger of intermittent, exertional hypoxemia. Previous research has revealed that hypoxia causes dysregulation of the endothelial L-arginine – dimethylarginine – nitric oxide pathway, causing excess hypoxic pulmonary vasoconstriction. We hypothesize that dysregulation of this important pulmonary vascular signalling pathway also affects the rate of decline of lung function and, by spillover of dimethylarginines from the pulmonary into the systemic circulation, triggers systemic co-morbidities, and thereby contributes to poor prognosis

The PROSA study sets out to investigate, by three different means, the prevalence of exertional desaturation in COPD patients at a relatively early stage. The 15-sec breath-hold test has been described to unveil sensitivity of COPD patients to intermittent hypoxemia [20]; it is an easily feasible and versatile test in clinical practice. The six-minute walk test certainly is the most often used exercise test in chronic diseases; it has been reported to generate a reliable diagnostic yield for exertional desaturation when continuous recording of SpO_2_ is performed [19]; therefore, it was selected as the primary determinant for stratification of COPD patients with or without exertional hypoxemia in the PROSA Study. Step tests on a bicycle ergometer cause the most effort in terms of personnel and equipment; however, this procedure can be expected to generate the best reproducibility of results; ergometer step tests have been shown to allow detection of exertional desaturation with continuous SpO_2_ recording in COPD patients [21]. In PROSA, all three approaches will be compared for their diagnostic sensitivities and specificities.

Non-invasive methods for assessing cardiac function, estimating pulmonary arterial pressure, and measuring systemic endothelium-mediated vasodilation will be applied to better understand the hemodynamic and vascular functional differences between COPD patients with and without exertional desaturation. This will be accompanied by biomarker measurements in blood samples taken throughout the study’s follow-up period of three years, allowing to keep a closer eye on the underlying biochemical mechanisms.

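### The only time-to-event method named that could cover COPD-related mortality is Kaplan–Meier, and the hazard ratios are to come from logistic regression: a minor mismatch of method and endpoint

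*Protocol article*

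**What the plan says.** The Study design section lists two separate mortality endpoints, both framed over time. Endpoint 1 is "The difference in all-cause mortality over time in COPD patients with exertional desaturation versus those without exertional desaturation". Endpoint 2 is "The difference in COPD-related mortality over time in COPD patients with exertional desaturation versus those without exertional desaturation". Follow-up is 36 months, with yearly visits.

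The Statistical analysis section names three things that bear on them:

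- "Survival analyses will be performed using Kaplan–Meier curves comparing patients with or without exertional hypoxemia". The same sentence goes on to curves split by ADMA and SDMA cut-offs. It names no endpoint for the curves.
- "Logistic regression will be used to assess the relationship between exertional hypoxemia and mortality".
- "Hazard ratios (HR) and 95% confidence intervals (CI) will be calculated by multivariable-adjusted logistic regression analyses".

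The article names no Cox model, cause-specific hazard model or cumulative incidence function.

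**The concern.** For all-cause death Kaplan–Meier is the right tool. For COPD-related death it is not, if the curve is read as a risk. A patient who dies of another cause can no longer die of COPD, yet Kaplan–Meier treats that patient as censored and still exposed to a later COPD death. One minus the curve then estimates COPD mortality in a setting where nobody dies of anything else. It exceeds the real probability whenever other-cause deaths occur.

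What is at stake is the absolute risk of COPD death in each group and the difference between them at 36 months. If desaturators have more COPD deaths, as the study hypothesises, the difference is stretched in the direction of the hypothesis.

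The hazard-ratio sentence compounds this. A logistic model of death by 36 months returns an odds ratio and ignores when the death occurred. As written, therefore, no stated model gives a valid hazard comparison for endpoint 2.

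**Working it through.** **Figure in the plan.** There is none to reproduce. The sample size of 148 was set for the FEV1 endpoint, and the article gives no mortality rate of any kind. All mortality inputs below are assumptions.

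**Inputs from the article.** Follow-up is 36 months. One third of 148 patients are expected to desaturate, so about 49 versus 99.

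**Assumptions.** 3-year all-cause mortality F is 10% in non-desaturators and 20%, 25% or 30% in desaturators. A constant share s = 0.5 of deaths is COPD-related in both groups.

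**Formulas.** With proportional cause-specific hazards:

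- true cumulative incidence of COPD death = s × F
- one minus Kaplan–Meier, other deaths censored = 1 − (1 − F)^s

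| F | True incidence | 1 − KM |
|---|---|---|
| 10% | 5.0% | 1 − 0.90^0.5 = 5.13% |
| 20% | 10.0% | 1 − 0.80^0.5 = 10.56% |
| 25% | 12.5% | 1 − 0.75^0.5 = 13.40% |
| 30% | 15.0% | 1 − 0.70^0.5 = 16.33% |

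| Desaturators vs others | True difference | KM difference | Excess | Ratio |
|---|---|---|---|---|
| 20% vs 10% | 5.00 points | 5.43 points | 0.43 | 1.085 |
| 25% vs 10% | 7.50 points | 8.27 points | 0.77 | 1.10 |
| 30% vs 10% | 10.00 points | 11.20 points | 1.20 | 1.12 |

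**Sampling error, 25% vs 10% case.** √(0.125 × 0.875/49 + 0.05 × 0.95/99) = √(0.002232 + 0.000480) = 5.2 points, before any drop-out. Expected COPD deaths are 49 × 0.125 ≈ 6 and 99 × 0.05 ≈ 5. The excess of 0.77 points is about one seventh of one standard error.

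**What drives the size.** Let c and o be constant annual hazards of COPD and other death over 3 years. Then 1 − KM = 1 − exp(−3c), and cumulative incidence = c/(c + o) × [1 − exp(−3(c + o))]. The relative overstatement depends almost only on o: about 1.5% at 0.01 per year, 3% at 0.02, 6% at 0.04, 9% at 0.06 and 15–16% at 0.10.

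**Unequal competing deaths are not needed.** Take o = 0.06 in both groups and c = 0.02 versus 0.04. The true incidences are 5.33% and 10.37% (difference 5.03 points from unrounded values). Kaplan–Meier gives 5.82% and 11.31% (difference 5.48 points). The difference is again about 9% too large, although other-cause hazards are identical.

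**Odds ratio versus hazard ratio, 25% vs 10%.** For all-cause death the odds ratio is (0.25/0.75)/(0.10/0.90) = 3.00, while the hazard ratio is ln 0.75/ln 0.90 = 2.73. For COPD death with s = 0.5 the odds ratio is (0.125/0.875)/(0.05/0.95) = 2.71, and the cause-specific hazard ratio is again 2.73. The near agreement in the second case comes from these inputs. The two are different quantities.

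**The case against.** A reader might infer that the plan commits to Kaplan–Meier for COPD-related death. It does not say so. The survival-analysis sentence names no endpoint, its biomarker half matches an endpoint on mortality in general, and the Discussion mentions only total mortality among the secondary clinical endpoints. All-cause death is a natural reading, and for that the method is sound. This stands, and it makes the point conditional.

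A reader might also infer that the plan expects more cardiovascular deaths in desaturators, so that the bias must be unequal. The Background says of hypoxia-driven mechanisms that "but they also promote systemic cardiovascular disease and mortality", and the Fig. 2 legend says that intermittent hypoxemia from sleep apnea "has been shown to act as a driver of rapid lung function decline, systemic cardiovascular co-morbidity, and excess mortality". These are mechanism and hypothesis. Neither gives a cause-specific death rate by desaturation group. The article does not define COPD-related death either, so some cardiovascular deaths might count as COPD-related and not compete at all. That stronger reading is not supported, and the calculation does not need it.

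Two technical objections also hold:

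- Censoring other-cause deaths is legitimate when cause-specific hazards are compared, by log-rank or Cox. The bias arises only when one minus Kaplan–Meier is read as an absolute risk.
- A logistic analysis of COPD death by 36 months, with vital status known, counts other-cause deaths as non-events and escapes this bias. It does not yield the announced hazard ratio, however, and it ignores time, which the endpoint does not.

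Finally, an unseen full protocol or SAP may settle the handling of competing deaths. That would be decisive if the point were only a missing detail. But the article itself names one time-to-event method, does not limit it to the endpoint it suits, and states that hazard ratios will come from a model that does not produce them.

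**Conclusion.** The point holds as a minor, conditional one. As written, Kaplan–Meier is the only named time-to-event method that could cover COPD-related mortality over time. Used for that endpoint with other deaths censored, it overstates absolute risk in both groups. The difference is overstated by roughly 9% to 12% under the assumed rates. That is under 1 point in the 25% versus 10% case and well within sampling error.

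These sizes rest on assumed death rates, a constant 50% COPD share and proportional cause-specific hazards. The direction of the bias in each group does not depend on them, provided other-cause deaths occur. The bias would be unlikely to change a conclusion drawn from about 11 COPD deaths, but it is systematic and easily avoided.

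The statement that logistic regression yields hazard ratios is wrong whichever endpoint the curves show.

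**What to change.** In the Statistical analysis section:

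1. State that the Kaplan–Meier curves are for all-cause death.
2. For COPD-related death, show the cumulative incidence function (Aalen–Johansen) by desaturation group, with non-COPD death as a competing event. Report the 36-month difference with a 95% confidence interval.
3. Replace the logistic-regression hazard ratio with a Cox hazard ratio, cause-specific for COPD-related death. If logistic regression is kept, call its result an odds ratio.

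The cost is a sentence or two and no new measurements beyond the date and cause of death that endpoint 2 already requires. The cumulative incidence may need software beyond the two packages named. The article reports recruitment as ongoing, so the change can be made before results are known.

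### If the ADMA and SDMA cut-offs come from a ROC analysis against death in this same cohort, the survival comparison has a false-positive rate of about 17–24%, not 5%

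*Protocol article*

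**What the plan says.** The relevant text is in the Statistical analysis section of the protocol article. It states: "Survival analyses will be performed using Kaplan–Meier curves comparing patients with or without exertional hypoxemia", and adds a second grouping, "with ADMA and SDMA above or below the cut-off value determined in receiver-operated curve (ROC) analyses". For effect sizes it says: "Hazard ratios (HR) and 95% confidence intervals (CI) will be calculated by multivariable-adjusted logistic regression analyses". The threshold for all tests is that p below "0.05 will be considered statistically significant". The only safeguard is this sentence: "A correction of p will be performed for multiple comparisons when adequate".

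The Study design section lists three biomarker endpoints for which a cut-off could be derived: prediction of exertional desaturation (endpoint 5), of the slope of lung function decline (endpoint 6) and of mortality (endpoint 7, "The sensitivity and specificity of plasma biomarkers at baseline to prospectively predict the mortality rate in COPD patients").

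For ADMA and SDMA the article gives no numeric cut-off, no literature source, no criterion for choosing the cut-off and no validation step. The desaturation threshold and the lower limit of normal for FEV1, by contrast, each carry a citation.

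**The concern.** A ROC cut-off is normally chosen because it separates patients with the outcome from those without. If that outcome is death, comparing survival above and below the cut-off in the same patients tests a split that was already picked to look good. The usual p-value assumes that the split was fixed beforehand. It is then too small, and the hazard ratio is too far from 1. Sensitivity and specificity read off the same sample may also be optimistic.

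The stakes are the biomarker conclusions. The article's Discussion says that predictive biomarkers could help with risk assessment in routine care and could point to treatment options. A chance finding with a hazard ratio of 2 or 3 would be a poor basis for either.

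**Working it through.** **Inputs from the article**
- 148 patients, with drop-out of up to 15% (148 × 0.85 = 125.8, about 126 completers).
- 36 months of follow-up.
- Significance level 0.05 for all tests.

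**Assumptions, because the article is silent**
- 3-year mortality of 5–30%.
- A two-sided log-rank test for the Kaplan–Meier comparison.
- The cut-off maximises Youden's J = sensitivity + specificity − 1.
- Higher marker values count as worse. The Discussion presents ADMA as a mortality marker.

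**Method.** The marker is simulated independently of survival, so the true hazard ratio is 1 and every rejection is false. Survival is exponential with censoring at 3 years. There are about 3,000 runs per scenario. The hazard ratio is the one-step log-rank estimate exp(U/V), where U is observed minus expected deaths and V its variance.

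**Step 1: reproduce the plan's 0.05.** With a median split, which uses no outcome data, rejection was 0.042–0.057 over all scenarios. The Monte Carlo standard error is √(0.05 × 0.95 / 3000) = 0.004, so this agrees with 0.05.

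**Step 2: cut-off from a ROC against death in the same patients (n = 148).**

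| Assumed 3-year mortality | Expected deaths (148 × mortality) | False positives, any cut-off | False positives, cut-off kept within 10th–90th percentile | Median HR (any / restricted) |
|---|---|---|---|---|
| 5% | 7.4 | 0.208 | 0.168 | 3.23 / 3.10 |
| 10% | 14.8 | 0.215 | 0.186 | 2.59 / 2.14 |
| 15% | 22.2 | 0.209 | 0.194 | 2.13 / 1.88 |
| 20% | 29.6 | 0.230 | 0.208 | 1.96 / 1.75 |
| 30% | 44.4 | 0.223 | 0.209 | 1.71 / 1.57 |

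With n = 126 the false-positive rate was 0.175–0.231 and the median hazard ratio 1.63–3.38. Further runs with 148 patients and mortality between about 8% and 20% gave 21–24% and median ratios of 1.9–2.9. The overall range of 17–24% is 0.168 / 0.05 = 3.4 to 0.24 / 0.05 = 4.8 times nominal. The rate barely depends on mortality; the spurious hazard ratio does, and is largest when deaths are few.

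**Step 3: direction left open.** If the analyst may call either high or low values worse, the rate is 0.33–0.40.

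**Step 4: cut-off from a ROC against desaturation.** Rejection was 0.046–0.053 and the median hazard ratio 0.97–1.01. In further runs where desaturation itself raised mortality two- to threefold, rejection was 4.8–6.2% and the ratio 1.1–1.2. The survival test is therefore essentially uninflated.

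**Step 5: a real effect is exaggerated too.** With a true log hazard ratio of 0.3 per SD and n = 148, the median estimate was 3.22 with a death-based cut-off against 1.68 with a desaturation-based one at 10% mortality, and 2.58 against 1.66 at 20%.

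**The case against.** The strongest objection is that the article does not say which outcome the ROC uses. Desaturation is a listed biomarker target (endpoint 5), the Discussion names it first among the biomarker aims, and the Statistical analysis sentence sets the biomarker split beside the hypoxaemia split. On that reading Step 4 applies and the survival test is close to nominal. This stands, and it makes the point conditional. It does not remove the point: the cut-off is specified for a survival analysis, endpoint 7 asks for sensitivity and specificity for mortality, and nothing in the text excludes the death-based reading.

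The simulated test is also not spelled out in the article. No log-rank test is named, and the hazard ratios are attributed to adjusted logistic regression without saying that the split marker is the covariate. This stands as an assumption about the size. The selection problem itself does not depend on which test follows.

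An article may leave the cut-off criterion and the bootstrap to a fuller plan. That is fair for those details. The point here is the stated rule, which feeds a ROC-determined cut-off into a test at 0.05. The multiplicity sentence is discretionary and speaks of multiple comparisons, not of cut-off selection.

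Three stronger readings may tempt a reader, and the documents support none of them:
- **An unconditional fourfold inflation.** The factor is about 1 for a desaturation-based cut-off.
- **A combined error rate for ADMA and SDMA as if independent.** The article says nothing about their correlation, and its multiplicity sentence could cover the testing of two markers.
- **The same inflation for endpoints 5 and 6.** Endpoint 6 is "The sensitivity and specificity of plasma biomarkers at baseline to prospectively predict the slope of lung function decline in COPD patients", which involves no survival test. Same-sample accuracy figures there may be optimistic, but that was not quantified.

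**Conclusion.** The concern holds in conditional form. If the ROC is run against mortality in these patients, with a Youden-type cut-off and the direction fixed, the survival comparison rejects a true null in about 17–24% of studies instead of 5%. The median hazard ratio under no effect is about 2 to 3 at roughly 8–20% assumed 3-year mortality, and about 1.6–3.4 over 5–30%. If the cut-off is derived against desaturation, there is essentially no inflation. As written, the plan allows either.

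The result rests on an assumed mortality, a two-sided log-rank test and a maximum-Youden cut-off. It concerns secondary analyses that the article presents tentatively, and the primary endpoint is unaffected. It is a low-cost improvement, not a flaw that endangers the study.

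**What to change.** Amend the Statistical analysis section as follows:

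1. Make the main biomarker–survival test a continuous term for ADMA and for SDMA, log-transformed and expressed per SD, in a Cox model.
2. Draw the Kaplan–Meier curves at the median or at a cut-off fixed before outcomes are known.
3. If a ROC cut-off is reported, name its outcome, label it exploratory, and give sensitivity, specificity and hazard ratio corrected by bootstrap or cross-validation, with the cut-off selection repeated in each resample. Do not attach an uncorrected p-value to that split.

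The cost is a change of wording and some resampling code. No extra patients, visits or samples are needed. Recruitment is reported as ongoing, with results expected in 2028, so the change can still be made ahead of the final data. The price is that no validated clinical cut-off can be claimed from this cohort alone.

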### Sample size discussion

Sample size estimation was based on analysis with repeated-measures 2-way ANOVA (baseline – 1 year – 2 years – 3 years). We assume that one third of our study cohort will experience exertional hypoxemia as reported in previous studies [22, 23], and we estimate that a 20% difference in the primary endpoint will be of clinical significance. To prove or dismiss the primary endpoint with α = 0.05 and a power of 0.90, a total sample size of 148 COPD patients stages 2–3, groups B and E according to the current GOLD guideline [7] will be included in this study after accounting for an expected drop-out rate of up to 15%.

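### Adjusted hazard ratios are assigned to logistic regression, so the adjusted mortality estimates would be odds ratios under the wrong name

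*Protocol article*

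**What the plan says.** The first secondary endpoint in the Study design section of the Protocol article is "The difference in all-cause mortality over time in COPD patients with exertional desaturation versus those without exertional desaturation". The second is the same comparison for COPD-related mortality. On follow-up the section says: "Patients will be recalled to the study site once per year for a total of 36 months of follow-up". The Sample size discussion allows for an "expected drop-out rate of up to 15" per cent.

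The Statistical analysis section makes three statements that bear on mortality:

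- "Logistic regression will be used to assess the relationship between exertional hypoxemia and mortality".
- "Survival analyses will be performed using Kaplan–Meier curves comparing patients with or without exertional hypoxemia". The same sentence adds curves by ADMA and SDMA above or below a ROC-derived cut-off.
- Directly after that: "Hazard ratios (HR) and 95% confidence intervals (CI) will be calculated by multivariable-adjusted logistic regression analyses".

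No Cox, discrete-time or other hazard model is named anywhere in the article.

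**The concern.** The named quantity does not come from the named model. A hazard ratio compares death rates among those still at risk, and estimating it needs each patient's time to death or censoring. Ordinary logistic regression takes a yes/no outcome and returns an odds ratio.

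Two things follow. First, the estimates labelled HR would be odds ratios, printed beside Kaplan–Meier curves that they do not summarise, and a reader could take them for hazard ratios or pool them as such. Second, logistic regression has no place for a patient who leaves before 36 months. In ordinary practice that patient is either counted as alive or deleted, and the two choices can give different answers.

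At stake are the adjusted estimates for secondary endpoints 1 and 2 and for the ADMA/SDMA survival analyses. In an observational cohort, readers are likely to rely on the adjusted estimate.

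**Working it through.** **The plan's own figure.** The article states no figure for mortality or for a hazard ratio. Its only computed figure is the total of 148, which was set for the FEV1 endpoint "with α = 0.05 and a power of 0.90". Its drop-out step is coherent (125 / 0.85 = 147.1, rounded up to 148). The point below does not depend on that total.

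**Inputs.** From the document: 36 months of follow-up, up to 15% drop-out overall, and one third of patients desaturating. Assumed, because the document gives none: three-year mortality p0 in non-desaturators, the true hazard ratio, and drop-out by group.

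**Step 1: complete follow-up.** With three-year risks p0 and p1 and proportional hazards:

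- HR = ln(1 − p1) / ln(1 − p0)
- OR = [p1/(1 − p1)] / [p0/(1 − p0)]

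| p0 | p1 | HR | OR |
|---|---|---|---|
| 10% | 20% | 0.2231/0.1054 = 2.12 | 0.2500/0.1111 = 2.25 |
| 20% | 40% | 0.5108/0.2231 = 2.29 | 0.6667/0.2500 = 2.67 |

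With the true HR fixed at 2 and p1 = 1 − (1 − p0)², the OR is 2.05, 2.11, 2.25 and 2.43 for p0 of 5%, 10%, 20% and 30%. The gap grows with mortality.

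**Step 2: with drop-out.** Take constant rates over 3 years: death λ = −ln(1 − p)/3 and drop-out γ = −ln(1 − d)/3. Then:

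- P(death observed) D = λ/(λ + γ) × [1 − exp(−3(λ + γ))]
- P(alive and in the study at 36 months) S = exp(−3(λ + γ))
- OR with drop-outs counted alive = [D1/(1 − D1)] / [D0/(1 − D0)]
- OR with drop-outs deleted = (D1/S1) / (D0/S0)

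Take p0 = 10% and true HR 2, so p1 = 1 − 0.9² = 19%.

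*15% drop-out in both groups.* S0 = 0.90 × 0.85 = 0.765 and S1 = 0.81 × 0.85 = 0.6885. D0 = 0.09243 and D1 = 0.17586.

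- Counted alive: (0.17586/0.82414) / (0.09243/0.90757) = 2.10
- Deleted: (0.17586/0.6885) / (0.09243/0.765) = 2.11

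*25% in desaturators, 10% in the others.* The overall figure is still 25/3 + 2 × 10/3 = 15%. S0 = 0.90 × 0.90 = 0.81 and S1 = 0.81 × 0.75 = 0.6075. D0 = 0.0950 and D1 = 0.16595.

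- Counted alive: (0.16595/0.83405) / (0.0950/0.9050) = 1.90
- Deleted: (0.16595/0.6075) / (0.0950/0.81) = 2.33

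**Step 3: check by simulation.** One million patients per scenario, one third exposed. The ratio of deaths per person-time, which uses time and censoring, was 2.02 with equal drop-out and 1.99 with unequal drop-out. The odds ratios were 2.12 and 2.14 with equal drop-out, and 1.88 and 2.31 with unequal drop-out. This agrees with step 2 within simulation error.

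**The case against.** A fair defence has several parts.

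- *The sentence does not mention mortality.* True, but it follows the Kaplan–Meier sentence directly, and the same section assigns logistic regression to mortality. The survival reading is sound.
- *Logistic regression can approximate a hazard ratio.* Pooled logistic regression on person-period records can, over short intervals. The article describes nothing of the kind.
- *The analysis plan may say more.* It may add detail, but this is a specification stated in the text, not a detail left out of it.
- *Time and censoring are not ignored.* A reader might infer that the whole survival analysis discards them. The Kaplan–Meier curves use both. The criticism applies only to the adjusted estimates, since the curves are unadjusted and give no hazard ratio.
- *The gap is small.* This largely stands where drop-out is equal and mortality is low. In the 10% mortality, HR 2 case with 15% drop-out in both groups, expected deaths are 49.3 × 0.17586 = 8.7 and 98.7 × 0.09243 = 9.1. The standard error of the log odds ratio is √(1/8.7 + 1/40.7 + 1/9.1 + 1/89.5) = 0.51. The 95% interval therefore spans a factor of exp(1.96 × 0.51) = 2.7 either way, which dwarfs a gap of 5 to 6%.
- *Logistic regression for mortality is legitimate.* This stands. The sentence linking exertional hypoxemia and mortality through logistic regression does not call its result a hazard ratio and is not wrong in itself.

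**Conclusion.** The point holds for the adjusted mortality estimates: secondary endpoints 1 and 2, and the ADMA/SDMA survival analyses. The wrong label and the mismatch of model and estimand are certain and rest on no assumption. The size of the numerical error is not certain. With true HR 2 and 10% control mortality it runs from about 5 to 6% (equal 15% drop-out) to an odds ratio of 1.90 or 2.33 (25% versus 10%). Under unequal drop-out its direction depends on how drop-outs are handled. The mortality rates and the drop-out split are assumptions.

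Three stronger readings are tempting but not supported:

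- *The mortality result will be materially biased.* Sizeable bias depends on unequal drop-out or high mortality, and the document gives neither.
- *Too few deaths will occur to adjust for more than one or two covariates.* The count depends on the assumed mortality. At complete follow-up, 10% versus 19% gives 148 × (2/3 × 0.10 + 1/3 × 0.19) = 19 deaths, and 20% versus 40% gives 148 × (2/3 × 0.20 + 1/3 × 0.40) = 39. No covariate limit follows from the document.
- *The study's main conclusion is at risk.* The primary endpoint is FEV1 decline, which this sentence does not touch.

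The error is confined to secondary estimates and is easily corrected before analysis, so it is a should-fix.

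**What to change.** Replace the sentence with: *Hazard ratios and 95% CIs will be estimated by Cox proportional-hazards regression, with follow-up censored at last contact or 36 months.*

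For COPD-related mortality, add how deaths from other causes are handled, for example a cause-specific hazard with censoring at other deaths.

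Logistic regression for 36-month vital status may stay as a complementary analysis. Its results should then be reported as odds ratios, with the handling of drop-outs stated.

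The cost is a few sentences of wording. SPSS 27, already named in the plan, fits Cox models, and no new data are needed. The article reports that recruitment is ongoing and results are expected in 2028, so the change can be made before the analysis.
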